## Abstract

**Background:**

The increasing age of the population, especially in the western world, means that the prevalence of osteoarthritis is also increasing, with corresponding socioeconomic consequences. Although there is no curative intervention at present, in accordance with US and European guidelines, pharmacotherapeutic and non-pharmacological approaches aim at pain control and the reduction of functional restriction.

It has been established that hydrotherapy for osteoarthritis of the hip or knee joint using serial cold and warm water stimulation not only improves the range of movement but also reduces pain significantly and increases quality of life over a period of up to three months. Weight reduction is important for patients with osteoarthritis of the hip or knee. In addition, conventional physiotherapy and exercise therapy have both been shown, at a high level of evidence, to be cost-effective and to have long-term benefits for pain relief, movement in the affected joint, and patient quality of life.

**Methods/design:**

The study design consists of a prospective randomised controlled three-armed clinical trial, which will be carried out at a specialist clinic for integrative medicine, to investigate the clinical effects of hydrotherapy on osteoarthritis of the knee or hip joint, in comparison with conventional physiotherapy.

One hundred and eighty patients diagnosed with osteoarthritis of hip or knee will be randomly assigned to one of three intervention groups: hydrotherapy, physiotherapy, and both physiotherapy and hydrotherapy of the affected joint. In the first group, patients will receive Kneipp hydrotherapy daily, with water applied in the form of alternate cold and warm thigh affusions (alternating cold and warm water stimulation is particularly relevant to the knee and hip regions).

Patients in the second group will receive physiotherapy of the hip or knee joint three times a week. Patients in the physiotherapy-hydrotherapy combination group will receive both joint-specific physiotherapy three times a week and alternate cold and warm thigh affusions every day. Follow-up assessments will be on three levels: clinical assessment by the investigator; subjective patient assessment consisting of a patient diary, and questionnaires on admission and at the end of the treatment phase; and a final telephone assessment by the external evaluation centre. Assessments will be made at baseline, after two weeks of inpatient treatment, and finally after a further ten weeks of follow-up. The primary outcome measure will be pain intensity of the affected joint in the course of inpatient treatment, judged by the patient and the investigator. Secondary outcomes include health-related quality of life and joint-specific pain and mobility in the course of the study. Statistical analysis of the results will be on an intention-to-treat basis.

**Conclusion:**

This study methodology has been conceived according to the standards of the CONSORT recommendations. The results will contribute to establishing hydrotherapy as a non-invasive, non-interventional, reasonably priced, therapeutic option with few side effects, in the concomitant treatment of osteoarthritis of the hip or knee.

**Trial Registration:**

***Trial registration number***: NCT 00950326

## Background

Osteoarthritis (OA) is the most common and most enduring physical impairment of patients in the western world; age is known to be one of the most important risk factors for this disease. It affects approximately 10% of all people over 60, with estimated socioeconomic consequential costs of about 60 billion dollars per year in the US alone [1].

As well as considering osteoarthritis to be a result of mechanical irritation, attrition and erosion of the cartilage matrix, another scientific hypothesis postulates a loss of vital cartilage cells and cartilage matrix degeneration [2]. Obesity, with a BMI >26, is considered a predictive marker for osteoarthritis of the knee or hip joint [3].

The clinical picture of osteoarthritis is characterised mainly by joint pain, crepitus, joint stiffness after rest, hyperthermia, and progressively restricted movement. Along with overweight, preventable or at least modifiable risk factors are physical activity, nutrition, and hormonal influences [4].

Although there is no curative intervention at present, in accordance with US and European guidelines, pharmacotherapeutic and non-pharmacological approaches aim to control pain and reduce reduction of functional restriction. Non-pharmacological therapy comprises a multidisciplinary approach consisting, for example, of instructions for weight loss and exercise therapy; pharmacotherapy comprises non-opioid analgesics, non-steroidal anti-inflammatory drugs (NSAIDs) including COX-2 inhibitors, topical analgesics (e.g. capsaicin cream), and opioid analgesics, as well as intra-articular steroid and hyaluronic acid injections [5].

Various epidemiological studies showed that NSAIDs were prescribed for 86.9% of patients, analgesics for 29.9% received, chondroprotectives for 7.6%, and gastroprotective drugs for 36.9% [6]. In just one year in France, 17 million prescriptions and five million days' absence from work were documented because of osteoarthritis [7].

NSAIDs have gastrointestinal side-effects, so complementary and alternative medicine (CAM) is increasingly offering concomitant therapeutic options. The prevalence of the use of CAM in osteoarthritis is estimated to be 40%: vitamin supplements, celery extract, fish oil, and garlic extract are often part of patient self-medication [8]. CAM further offers evaluated therapeutic procedures, including acupuncture, various herbal agents such as stinging nettle, boswellic acid, devil's claw extract, and proteins such as glucosamine [9,10]. Besides acupuncture and glucosamine, systematic reviews have also evaluated pool therapy, balneotherapy, thermotherapy, and exercise therapy, and found beneficial outcomes for pain and movement restriction in osteoarthritis of the hip or knee [11-14].

Patient surveys showed that 80% of patients with osteoarthritis had used several complementary medical procedures in the previous month; 52% used over the counter medicines. Other approaches taken were dietary measures (71.5%); mind-body techniques (42.4%), salves and ointments and other topical applications (38.1%), taking vitamins and/or trace elements (32.9%), herbal preparations, and various physical manipulation techniques (21.4%) [15].

Several basic articles describe Kneipp hydrotherapy (e.g. in the form of alternate cold and warm thigh affusions) as having an active effect on the vessels by causing initial local vasoconstriction followed by reflexive vasodilatation, which activates the cutaneous circulation [16-18]. Furthermore, modulation of hormone production was scientifically demonstrated for cortisol and adrenaline [19-21].

Immunologically, hydrotherapy increases serum concentrations of alpha-2 macroglobulin, IgM antibodies, and complement factor C3 [22]. In addition, using alternate cold and warm back affusions, positive effects were found on immunoregulation, in the sense of an increase in resistance and facilitated activation of cell-mediated (Th1) immune reactions, as measured by the mediating cytokines IFN-gamma and IL-2 [23].

Serial cold and warm water stimulation hydrotherapy for osteoarthritis of the hip or knee joint showed improvement of restricted joint mobility, along with significant pain reduction and increase in quality of life over a period of up to three months [24,25].

In particular, serial application of alternate cold and warm thigh affusions (Figure 1) has established itself as concomitant therapy for osteoarthritis of the hip or knee; this therapeutic application is also indicated for adjuvant treatment of peripheral arterial disease and insomnia. The thigh affusion is poured starting from the back of the foot up the outer aspect of the back of the leg, slowly over the buttocks ("starting away from the heart going towards the heart"), from there moving to the front aspect of the leg, lingering in the groin, and finally pouring the water over the inner aspect of the leg downwards [26].

**Figure 1 F1:**
[figure not shown]
**Alternate thigh affusion according to Kneipp – flow direction (repeated cold/warm water stimulation)**. The thigh affusion is poured starting from the back of the foot up the outer aspect of the back of the leg, slowly over the buttocks ("starting away from the heart going towards the heart"), from there moving to the front aspect of the leg, lingering in the groin, and finally pouring the water over the inner aspect of the leg downwards.

Weight reduction is important for patients with osteoarthritis of the hip or knee. In addition, conventional physiotherapy and movement therapy have both been shown, at a high level of evidence, to be cost-effective and to have long-term benefits for pain, movement in the affected joint, and patient quality of life [27-29].

This randomised clinical trial will be funded by the Otto Schönfisch Foundation, Bad Wörishofen, Germany (Project number: Dr.Wa/zie/2.7.08).

## Methods/design

### Research aims and questions

The main aim of this three-armed clinical study will be to determine the effects of hydrotherapy with alternate cold and warm affusions of the thigh in the concomitant treatment of osteoarthritis of the hip or knee. The main outcome measures are pain reduction, improvement in the quality of life, and increased movement in the affected joint.

### Research questions

1. Does Kneipp hydrotherapy show a measurable effect in the sense of altered clinical findings in the affected knee or hip joint?

2. How effectively does hydrotherapy influence the clinical parameters of pain, range of movement, and function of the affected joint?

3. How effectively does hydrotherapy affect the secondary outcome measures of quality of life, pain experienced, mood, and blood pressure?

4. Do hydrotherapeutic applications simply provide short-term therapeutic success or are there long-term changes in the clinical findings?

5. Are the clinical effects of hydrotherapy comparable with those of conventional physiotherapy of the affected joint?

6. Are the clinical effects of hydrotherapy used as monotherapy comparable with a combination of hydrotherapy and physiotherapy of the affected joint?

7. Do unwanted effects or side effects occur with hydrotherapy?

### Study duration

January 2009 – December 2010

### Design

This study was designed as a prospective randomised controlled clinical trial with three arms, which is to be carried out at a German clinic specialised in integrative medicine, to investigate the clinical effects of hydrotherapy on osteoarthritis of the knee or hip, as compared with conventional physiotherapy.

To achieve maximum scientific accuracy with respect to randomisation, random distribution, avoidance of selection bias, etc., the independent Department of General Medicine and Primary Care of the University of Leipzig Medical School will function as an external evaluation and testing centre.

The design and concept of this study, as well as its ethical validity, were reviewed and approved by the Ethics Committee of the Bavarian State Chamber of Physicians [Ethikkommission der Bayerischen Landesärztekammer], (Study Number 08032, dated 04.05.2008).

### Subjects

All patients of a German clinic for integrative medicine who have symptomatic osteoarthritis of the hip or knee joint, who meet the revised criteria of the American College of Rheumatology, who have agreed to participate in the study, given their informed consent and signed a data privacy policy statement, will be included in the study. Patients will be given an information sheet, which will tell them they will be randomly assigned to one of the three following treatment groups:

**In group 1**, patients will receive a specific hydrotherapeutic procedure in the form of alternate cold and warm thigh affusions (pouring on water) which will consist of repeated cold and warm water stimulation of the knee and hip region. Physiotherapy of other regions, such as the back, is permitted but there will be no specific physiotherapy of the hip or knee joint.

**In Group 2**, patients will be given physiotherapy of the hip or knee joint three times a week but no thigh affusions. Affusions of other regions, such as the back, are permitted.

**In Group 3**, patients will receive not only joint-specific physiotherapy of the hip or knee joint but also daily thigh affusions of alternate cold and warm water.

The patients will be informed of possible unwanted side-effects; in addition they will be told that they can withdraw from the study at any time without any fear that they will not continue to receive treatment.

The inclusion and exclusion criteria are to be found in Table 1.

**Table 1 T1:** Eligibility criteria

**Inclusion criteria**	
1	Age ≥ 18 years
2	Symptomatic osteoarthritis of hip or knee (following the revised criteria of the American College of Rheumatology)
3	Willingness to comply with follow-up assessments and treatment
4	Ability to understand, read and speak German

**Exclusion criteria**	

1	Endoprothetic replacement of hip or knee joint
2	Inflammatory arthropathy of the hip or the knee
3	Acute, hot, red and swollen knee or hip joint (unknown focus)
4	Inflammatory system diseases which could interfere with the evaluation of the therapy procedure
5	CNS diseases, especially epilepsy
6	Anamnesis of deep vein thrombosis in the past 12 months
7	Severe lung disease such as e.g. COPD stages GOLD III – GOLD IV
8	Heart failure NYHA III – NYHA IV
9	Myocardial ischemia with or without intervention within the last 3 months before inpatient admission
10	Cancer in advanced stage
11	Large skin wounds or inflammatory and ulcerated dermatosis of the legs
12	Severe febrile infectious diseases Non treated hypertension
13	Participation in another clinical study within the past four weeks
14	Pregnancy

After the treating physician has clinically examined a patient with osteoarthritis of the hip or knee and confirmed that all the inclusion criteria and none of the exclusion criteria are met, the patient will be given the information sheet, a statement of informed consent, and a privacy policy statement for this clinical study. If the patient agrees to take part, the external evaluation centre will be informed, and will send the investigator a plain envelope with a randomisation number, treatment group assignment, and the necessary study documents.

### Randomisation and treatment allocation

Based on the results of a pilot study, a randomisation number list and treatment group assignment has been generated by software before the beginning of the main study. When the envelope is opened, the investigator and patient will come to know the treatment group assignment (group 1, 2, or 3) with a corresponding treatment plan in line with the study protocol, the patient diary for the inpatient treatment phase, and all the necessary assessment forms for both doctor and patient.

Prior to the study, all medical specialists in the clinic and attending therapists have been given a briefing on the study protocol, the ethical basis of this clinical study, the randomisation procedure, and the specific therapy for each treatment group, in line with the study protocol.

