**Figure 2 F2:**
[figure not shown]
**Flowchart describing the participant flow through the study**. Diagramm over the participant flow through recruitment, randomization, baseline measurement, post-treatment and 3 month follow-up.

During the clinical phase the following interventions will be applied:

In **intervention group 1**, the patient will receive hydrotherapy appropriate for osteoarthritis of the hip or knee, in the form of daily thigh affusions of alternate cold and warm water. In this group, physiotherapy may also be given but not specifically for the affected hip or knee joint.

In **intervention group 2**, patients with osteoarthritis of the hip or knee will receive specific physiotherapy of the affected hip or knee joint three times a week, but **without **any disease-specific hydrotherapy. Because of the holistic approach of the clinic, however, these patients will still receive hydrotherapy at sites other than the affected joint, for example, alternate cold and warm affusions of the back or an ascending lumbar affusion.

In **group 3, the control group**, patients with active osteoarthritis of the hip or knee will receive specific, joint-related hydrotherapy in the form of a (daily) alternate cold and warm thigh affusions **as well as **joint-specific physiotherapy (three times a week).

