### Diagnostic and biometric evaluation procedure

Each patient will undergo a medical examination at the time of admission and a final examination after two weeks of inpatient therapy, in which the general physical state and disease-specific previous medication and therapy will be documented. At the two medical examinations, pain intensity will be measured on a ten-point visual analogue scale, and 1) diagnostic assessment of the affected joint according to the neutral-zero method (hip joint: flexion and extension, internal and external rotation; knee joint: flexion and extension); 2) the timed "up and go" (TUG test) as an indirect assessment criterion of flexion and extension in the affected hip or knee joint; and 3) the body mass index (BMI) will be recorded in the case report form or physician's questionnaire.

**Independently of the doctor**, a standardised questionnaire will be filled out by the patient at the time of admission and after two weeks of inpatient therapy. These questionnaires will be sent to the evaluation centre directly after they are handed in.

The same assessment will be carried out in a telephone interview by the external study centre, ten weeks after the end of inpatient care.

The assessment includes A) the SF-36 test, B) the Lequesne hip or knee questionnaire, C) the AIM-2-SF Scales 2 Short Form, and D) the EQ-5D test.

In addition, each patient will be given a diary for self-reporting during inpatient treatment. This diary will be completed by the patient: it contains the subjective visual analogue scale, the current mental health state scale of the EQ-5 D test, and blood pressure measurements (filled out by the nursing staff) ((Figure 3)).

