### Outcome measures

#### Primary outcome measure

The primary outcome measure will be the pain intensity of the affected joint during inpatient care, as assessed by the patient and the investigator. The patient rates subjective pain intensity in the patient diary on a ten-point visual analogue scale (0 = no pain; 10 = greatest pain imaginable); the doctor also records pain intensity around the affected joint on a ten-point visual analogue scale. The use, practicality, and validity of visual analogue scales have been sufficiently evaluated and are scientifically accepted [30,31]

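### Baseline forms and diary arrive in the envelope that reveals the arm, so baseline ratings, as described, are open to knowledge of the allocation

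*Protocol article*

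**What the plan says.** After the eligibility examination and consent, the evaluation centre "will send the investigator a plain envelope with a randomisation number, treatment group assignment, and the necessary study documents" (text after the exclusion criteria, Table 1). The section Randomisation and treatment allocation says who learns the arm: "When the envelope is opened, the investigator and patient will come to know the treatment group assignment (group 1, 2, or 3". The same sentence lists what else comes to hand at that moment: "the patient diary for the inpatient treatment phase, and all the necessary assessment forms for both doctor and patient". No exception is made for baseline forms.

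The Figure 2 caption gives the order as "participant flow through recruitment, randomization, baseline measurement, post-treatment and 3 month follow-up".

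Under Diagnostic and biometric evaluation procedure, the physician's part reads "At the two medical examinations, pain intensity will be measured on a ten-point visual analogue scale". These examinations are at admission and after two weeks, and the results go into the case report form or physician's questionnaire. For the patient, "a standardised questionnaire will be filled out by the patient at the time of admission and after two weeks of inpatient therapy". This is described as independent of the doctor, which is not the same as independent of the allocation.

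The primary outcome is subjective and has two raters: "The primary outcome measure will be the pain intensity of the affected joint during inpatient care, as assessed by the patient and the investigator". The Statistical analysis section plans a repeated-measures ANOVA for it. Baseline adjustment is foreseen only if the groups turn out to be inhomogeneous.

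**The concern.** Both raters of the primary outcome learn the arm when they receive the forms. In a clinic known for hydrotherapy, a patient who has just learned that affusions will or will not be given may rate pain differently, and so may an investigator with expectations. Baseline is one side of every change over time, so a shift confined to one arm's baseline can pass for a treatment effect or hide one. A baseline that may already depend on the arm is also an unsafe covariate. The Sample size section aims the trial at an interaction between the groups, which is the kind of contrast exposed here.

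**Working it through.** **1. Order of events.**
- Text after Table 1: examination, then consent, then an envelope with allocation and study documents.
- Randomisation and treatment allocation: opening it reveals the arm and delivers the diary and all assessment forms.
- Figure 2 caption: randomisation, then baseline measurement.
- Diagnostic and biometric evaluation procedure: baseline at admission, not placed before or after opening.

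The first three agree, and the fourth does not contradict them. The inference is strongest for the diary and patient questionnaires. It is weaker for the physician's values, because an examination takes place before allocation and the article does not say whether it is also the admission examination.

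**2. Bias formula.** Let knowledge of the arm shift one arm's baseline by b and its later ratings by s. With two occasions the group-by-time contrast is the difference in mean change:

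bias = s − b.

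If s = 0 the bias is −b, the whole baseline shift. If s = b it cancels. Steps 3 to 5 take s = 0.

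**3. Illustration, pairwise comparison.** The document gives 180 patients and three arms. Equal allocation is assumed: 180/3 = 60 per arm. The SD of change (2 to 3 points on the 0–10 scale) and b are assumptions; the article gives neither. SE = SD × √(2/60), noncentrality = b/SE, two-sided 5% t-test with 118 df, no true effect:

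| b | SD of change | SE | b/SE | Rejection |
|---|---|---|---|---|
| 0.5 | 2.0 | 0.365 | 1.37 | 27% |
| 0.5 | 2.5 | 0.456 | 1.10 | 19% |
| 0.5 | 3.0 | 0.548 | 0.91 | 15% |
| 0.25 | 2.0 | 0.365 | 0.68 | 10% |
| 0.25 | 2.5 | 0.456 | 0.55 | 8% |
| 0.25 | 3.0 | 0.548 | 0.46 | 7% |

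**4. Illustration, three-arm group-by-time test.** Simulation with 4,000 runs per setting, 60 per arm, an assumed SD of 2 points at each occasion, pre-post correlation rho, b = 0.5 in one arm and no true effect:

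| rho | Pre-post bias | Rejection | ANCOVA bias | Rejection |
|---|---|---|---|---|
| 0.3 | −0.50 | 20% | −0.14 | 7% |
| 0.5 | −0.49 | 26% | −0.24 | 11% |
| 0.7 | −0.50 | 42% | −0.35 | 25% |

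With b = 0 the bias is about 0 and the pre-post test rejects in 4.7–5.4% of runs. ANCOVA passes on about rho × b: 0.5 × 0.5 = 0.25, against 0.24 simulated. In these runs the planned comparison of baseline characteristics flags the 0.5-point shift in only 26–28% of trials, so the conditional adjustment would usually not be triggered.

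**5. Daily diary.** If m equally spaced entries are summarised by a linear trend, the share of a first-entry shift carried into the fitted total change is 6(m − 1)/(m(m + 1)). For m = 2 this is 6/6 = 100%. For m = 14 it is 78/210 = 37%, and for m = 15 it is 84/240 = 35%. A change measured from the first entry still carries the whole shift.

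The plan's own figure of 180 at 95% power cannot be reproduced, because the article does not state effect size, correlation or number of occasions. The point does not depend on it.

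**The case against.** The article says what the envelope contains, not when each form is filled in. The physician examines the patient before consent. If pain, range of motion and the timed walking test were taken then, they could predate the envelope and be copied to the form later. Figure 2 is not shown, and a caption that summarises flow is not a procedural instruction. A full protocol or site instruction might fix the order.

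The arithmetic is also a special case. The same unblinded raters give the later scores, so a constant reporting shift (s = b) would cancel in the change. Shift, SD and arm size are assumed, and the pairwise t-test is not the planned three-arm analysis.

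Much of this stands. A reader might infer that no baseline value can be recorded before the arm is known; for the physician's values the documents do not support that. A reader might also infer that the analysis always passes the shift on in full. That holds only for two-occasion or change-from-first-entry contrasts with no matching later shift.

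Two things survive. The article does not merely leave the order out: it puts all forms in the unblinding envelope, and its caption points the same way. And cancellation cannot be relied on, since nothing ensures that s equals b.

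**Conclusion.** The point holds as an avoidable, unprotected risk. Followed as written, the plan has baseline pain and the patient questionnaires recorded with the arm known, and the physician's measures too unless they come from the examination before consent. The consequence ranges from the whole unmatched shift (two-occasion contrast), through about rho times it (ANCOVA), to roughly 35–37% of it (linear trend over 14–15 daily entries). The 15–27% error rate for a 0.5-point shift and the 7–10% for a 0.25-point shift rest wholly on the assumed shift, an SD of change of 2 to 3, 60 per arm and no shift in later ratings. They show sensitivity; they do not estimate this trial's error rate. The documents give neither size nor direction, so a demonstrated bias should not be read into this. The conditional adjustment would not reliably detect the shift and would not fully remove it.

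**What to change.** Supply the baseline physician form, the baseline patient questionnaire and the first diary pain score as a separate packet that carries no allocation and is held at the clinic. Require that it is completed, dated and closed before the envelope is opened. State the order as consent, baseline, randomisation, treatment, and align the Figure 2 caption and flow with it. If the physician's values are meant to come from the examination before consent, the text should say so.

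The cost is repackaging existing forms and a sentence of procedure: no extra visit, staff or patients, and no change to the sample size. Post-treatment ratings remain unblinded, so their own reporting bias (s above) stays and should be named as a limitation.
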